### Recruitment

Patients of public hospitals in Australia (Royal Women’s Hospital, Mercy Hospital for Women, Joan Kirner Sunshine Hospital Western Health and Royal Prince Alfred Hospital) and at Hassadah Medical Centre (Jerusalem, Israel), along with patients receiving care at private institutions (Ramsay Health, Epworth HealthCare, Melbourne IVF, NewLife IVF, Fertility (Sydney CBD and Melbourne CBD), Genea Fertility and private consulting rooms of affiliated gynaecologists) are screened for eligibility. Accredited study team members (gynaecologists, gynaecology trainees and research nurses/assistants) will screen outpatient clinic lists, surgery waiting lists and medical records, and identify patients during consultations, and preadmission clinics. Eligible participants may be approached in person, by phone or email; treating clinicians may record verbal expressions of interest and refer these to research nurses/assistants, who will confirm eligibility, manage consent and oversee recruitment. Advertising material describing the project is available in waiting rooms of participating hospital clinics and private gynaecologists’ rooms. A website (https://www.endometriosis.org.au) enables patients to access information about the study online and to enquire about eligibility.

Potential participants are provided with written and verbal information about the study. Those wishing to participate will provide consent either in written form or via an online consent managed by REDCap (Research Electronic Data Capture; Vanderbilt University, Nashville, Tennessee, USA).^29
30^ Individual consent is obtained from each participant prior to any information being gathered. Consent from male partners is requested, recognising the potential for comorbid male-factor infertility. If indicated, semen analysis reports will be sought as additional data.

### Sample selection: inclusion and exclusion criteria

#### Inclusion criteria

≥18 years and <38 years of age at time of recruitment. These age restrictions were made due to (a) jurisdictional issues with the recruitment of minors and (b) local and international practices where ART is more likely to be recommended to women of advanced age seeking conception, irrespective of the cause of the infertility.Desire for fertility (current or future) including women with infertilityEMSE—defined asUltrasonically (expert tertiary level sonologist) or MRI diagnosed endometriosis includes current presence of:An ovarian cyst with ground-glass appearance that is the same size or larger on repeat imaging 4 weeks or more apart.Deep infiltrating endometriosis (deep to peritoneum) or other hallmarks (such as obliterated Pouch of Douglas) as diagnosed on ultrasound or MRI by a practitioner with the required skills.Presence of untreated moderate or severe endometriosis (rASRM stages 3 or 4) on a previous diagnostic laparoscopy/laparotomy.Own and use a mobile phone.

#### Exclusion criteria

Unable to understand and fully comprehend consent information.Do not wish to have future fertility.Findings suspicious of malignancy on expert imaging.Current pregnancy.

At the time of protocol development, no validated non-surgical preoperative grading system existed; the sonographic #ENZIAN classification was only published and validated in 2021. Because diagnostic laparoscopy without treatment is uncommon in clinical settings and requiring surgical confirmation would have severely limited recruitment, a pragmatic decision was made to use expert pelvic ultrasound and/or MRI to identify participants with imaging evidence of moderate–severe disease. We acknowledge that applying rASRM^5^ criteria to imaging is not validated and is a limitation; however, we minimised misclassification through strict imaging-provider protocols and predefined imaging criteria for moderate–severe endometriosis, and we will analyse the surgical subgroup to confirm concordance with rASRM stages 3–4, which will support the validity of our imaging-based cohort.^31^

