#### Study groups

Participants are allocated to one of two management groups prior to conception: a preconception surgery group (n=350) or a planned non-surgical (conservative) management group (n=350). Within each management group, participants will be subdivided by conception method into a natural conception subgroup (n=200 in each of the surgical and conservative management groups) and an ART (ART/IVF) subgroup (n=150 per preconception management group). Participants may contribute multiple attempted conception cycles, and to both natural and ART cycles.

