Menstrual-cycle symptoms are measured using a simple, 4-point Verbal Rating Scale (VRS) for pain intensity (no pain/mild pain/moderate pain/severe pain) accompanied by pictograms to improve respondent interpretation and reduce response burden. VRSs are widely used and have demonstrated acceptable validity and reliability for clinical pain intensity assessment compared with other pain measures (eg, Visual Analogue and Numeric Rating Scales) and are well suited to brief, repeated measurement in field studies.^32^ A brief 4-point VRS was included rather than longer symptom inventories because more comprehensive menstrual symptom instruments (eg, the Menstrual Distress Questionnaire and other multi-item menstrual symptom scales) are lengthy and were not feasible for monthly administration in a fertility cohort in which the principal outcomes are reproductive.^33^ The questionnaire items and the VRS pain measure were selected to maximise face validity, minimise respondent burden, and enable longitudinal linkage of symptom reports to timing of intercourse, ovulation windows, pregnancy test results and pregnancy outcomes.

The accuracy of participant-entered clinical data is safeguarded by the structured nature of the study-specific questionnaires and real-time front-end checks to prevent entry errors, automated rules that flag implausible or inconsistent responses for in-app confirmation and staff follow-up for clarification. Where participants consent, medical records will be reviewed to verify key outcomes such as surgical reports. For those undergoing surgery during the study period, surgical reports will be collected and assessed by one of two investigators (SM and VR); any disagreements will be clarified by investigator MH. The primary outcome, LBR, is assessed by patient reported data (via the ELFS App) and cross-validated against obstetric outcome data retrieved from the hospital in which the birth occurs. Similarly, CPR is assessed by patient report, and validated by review of first trimester sonographic report. Sensitivity analyses excluding unverified outcomes and analyses of agreement with medical records may be required. Reassuringly, several studies have supported the ability of patients to accurately report their reproductive history, particularly with regards to surgical interventions, fertility treatments and pregnancy outcomes.^34
35^

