While these trials will provide important randomised evidence on surgery versus ART in selected infertile or high-risk groups, their restrictive eligibility, omission of natural conception arms and lack of systematic assessment of comorbid adenomyosis limit generalisability. Moreover, these three study designs anticipate that participants will be willing to be randomised despite the scientific equipoise. Many patients with severe endometriosis, even in the absence of colorectal or urological obstruction (both of which are exclusion criteria in these randomised trials), will be highly symptomatic, and despite fertility desires, will actively pursue surgery in the hope of symptom control. These studies underscore the need to also measure natural time-to-pregnancy and spontaneous conception rates, and to adopt a broader, real-world design that captures symptom burden and patient treatment preferences alongside fertility outcomes.

Alongside these important ongoing randomised studies, ELFS aims to compare fertility outcomes for those who have moderate or severe endometriosis pursuing either natural or ART conception, including both those who undergo preconception surgery and those who are conservatively managed, with cross-comparisons between all four groups. The large sample size and pragmatic observational approach have, to date, demonstrated feasible recruitment.

This study has several important potential limitations. The primary outcome requires a large participant sample, but strict inclusion criteria to ensure accurate diagnosis of moderate and severe endometriosis may considerably restrict the eligible population. This could slow recruitment, reduce statistical power if target numbers are not met, and introduce selection bias, which in turn may limit applicability beyond specialist endometriosis care settings.

Furthermore, the repeated collection of sensitive data, including sexual history, fertility and pregnancy outcomes, may negatively affect participant experience and engagement. The burden and intrusiveness of such assessments could lead to distress, underreporting of sensitive information, and differential loss to follow-up, with potential for missing and biased data. Together, these factors may affect both the internal and external validity of the study’s findings.

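### Agreement with surgical stage will be measured only in operated women, so it cannot vouch for imaging-defined women in the conservative group

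*Protocol article*

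**What the plan says.** All statements are in the protocol article.

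- **Exclusion criteria** (the paragraph after the list). Expert imaging was used because requiring surgical confirmation would have restricted recruitment. The authors are open about the weakness: "We acknowledge that applying rASRM^5^ criteria to imaging is not validated and is a limitation". They say that "we minimised misclassification through strict imaging-provider protocols and predefined imaging criteria for moderate–severe endometriosis", and then give the empirical safeguard: "we will analyse the surgical subgroup to confirm concordance with rASRM stages 3–4, which will support the validity of our imaging-based cohort".
- **Inclusion criteria.** Imaging entry can rest on a ground-glass ovarian cyst that persists on repeat imaging, or on deep disease or other hallmarks such as an obliterated pouch of Douglas. A separate, non-imaging route is "Presence of untreated moderate or severe endometriosis (rASRM stages 3 or 4) on a previous diagnostic laparoscopy/laparotomy". The Exclusion criteria section notes that "diagnostic laparoscopy without treatment is uncommon in clinical settings", so few women should enter that way.
- **Interventions.** The source of operative findings is limited: "For those undergoing surgery during the study period, surgical reports will be collected and assessed by one of two investigators". No corresponding check is described for imaging-defined women who are never operated on.
- **Study groups.** The plan is for 350 women with surgery and 350 managed conservatively.
- **Discussion.** Many patients with severe disease "will be highly symptomatic, and despite fertility desires, will actively pursue surgery in the hope of symptom control".

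**The concern.** Concordance among operated women estimates the positive predictive value of imaging in women who ended up having surgery. The article uses it to support the imaging-based cohort as a whole, half of which is planned to be managed without surgery. This is partial verification: the reference standard reaches only those selected for it.

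The result carries over only if, among women with the same imaging, having surgery is unrelated to true stage. The article gives reasons for doubt. Symptoms and preference influence who has surgery, and the entry criteria differ in kind, so the two groups may have entered on different evidence.

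What is at stake is what the study may say about its comparator. If imaging is wrong more often in the conservative group, and women wrongly classified have a different live birth rate, the contrast between groups mixes a difference in disease with the effect of surgery. The planned check would look equally good whether or not that had happened.

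**Working it through.** The plan gives no concordance figure to reproduce, so the check is an argument from the text followed by an illustration.

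**1. What the check estimates.** Let c_k be the proportion with confirmed stage 3–4 among operated women who entered on imaging criterion k, and let s_k be the share of operated imaging-entry women with that criterion. Then

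pooled concordance = Σ s_k × c_k.

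To apply to the conservative group, two conditions are needed: the shares s_k must be the same there (or the c_k all equal), and each c_k must be the same in women who were not operated on. The first can be examined from recorded imaging. The second cannot be tested with the data described.

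**2. What the check can see.** If the predictive value is P_S in the surgical group and P_C in the conservative group, the planned analysis returns an estimate of P_S. P_C does not enter it.

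**3. What a gap could do.** Inputs:

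- live birth rate per cycle in true stage 3–4 disease: 1.4% (Power calculation and planned analysis, natural conception)
- rate in women without stage 3–4 disease: 4%, *assumed*; the article gives none
- P_S = 90%, *assumed*
- P_C from 95% down to 70%, *assumed*
- no true effect of surgery

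Group rate = P × 1.4% + (1 − P) × 4%.

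Surgical group: 0.90 × 1.4 + 0.10 × 4 = 1.66%.

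| P_C | Conservative rate | Null rate ratio (surgery / conservative) | Concordance the check reports |
|---|---|---|---|
| 95% | 0.95 × 1.4 + 0.05 × 4 = 1.53% | 1.66 / 1.53 = 1.08 | 90% |
| 90% | 1.66% | 1.00 | 90% |
| 85% | 0.85 × 1.4 + 0.15 × 4 = 1.79% | 1.66 / 1.79 = 0.93 | 90% |
| 80% | 0.80 × 1.4 + 0.20 × 4 = 1.92% | 1.66 / 1.92 = 0.86 | 90% |
| 70% | 0.70 × 1.4 + 0.30 × 4 = 2.18% | 1.66 / 2.18 = 0.76 | 90% |

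The last column never changes. The ratio moves either way with P_C, and would stay at 1.00 throughout if misclassified women had the same live birth rate as true cases.

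**4. Other assumed inputs.** Take P_S = 95% and P_C = 75%, with no surgery effect.

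- Natural conception, misclassified women at 2 times the 1.4% rate: (0.95 × 1.4 + 0.05 × 2.8) / (0.75 × 1.4 + 0.25 × 2.8) = 1.47 / 1.75 = 0.84. At 3 times: 1.54 / 2.10 = 0.73.
- IVF, base rate 12% (same section), misclassified women at 1.5 times: (0.95 × 12 + 0.05 × 18) / (0.75 × 12 + 0.25 × 18) = 12.3 / 13.5 = 0.91. At 2 times: 12.6 / 15.0 = 0.84.

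Here the check would report 95% in every case.

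**The case against.** The case for the plan has real force.

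- *The limitation is declared.* The sentence that describes the check also says that rASRM on imaging is unvalidated, and it claims support, not proof. This stands: a reader might infer that misclassification is being concealed, and the text does not bear that out. What goes unseen is narrower, namely the conservative group's own error rate.
- *The check feeds no primary estimate.* Entry is defined identically for both groups, and nothing in the planned analysis uses the concordance result. This stands. Any difference in true severity would be confounding. Neither stage nor imaging severity is named in the adjustment list, but that list is not exhaustive.
- *Selection on accuracy is inferred.* The Discussion speaks of symptoms and preference, not of imaging error, and the Introduction also describes women without much pain who might have surgery for fertility alone. This stands as to direction. It does not rescue the inference, which needs selection to be unrelated to true stage.
- *The illustration is assumed.* The 4% is the article's threshold for a worthwhile improvement, not a rate in milder disease. The 1.4% comes from women with 12 months of unsuccessful trying, while the cohort is broader. This stands, which is why a range is shown.

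Two further readings are tempting. One is that the check is circular because women staged at an earlier laparoscopy would agree automatically. But the check is tied to the imaging-based cohort, which most naturally leaves them out, and the article calls that route uncommon. If they were 10% of those checked, a true 80% would read as 0.10 × 100 + 0.90 × 80 = 82%. The other is that operated women found to have lower-stage disease will be dropped from the comparison. The article proposes no such exclusion.

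**Conclusion.** The point holds in a limited form. Concordance in operated women is informative about operated women. It does not, pooled and unadjusted, support the classification of never-operated women in the conservative group, and it cannot show a higher error rate there. The wording also presumes a favourable result before the data are in.

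A reader might go further and conclude that the comparison is biased against surgery by about a quarter (the 0.76 row). The article does not support that: it gives no predictive value for imaging in either group and no live birth rate for misclassified women. The range of 0.93 to 0.76 rests wholly on assumed inputs and shows only that a moderate gap in accuracy could matter and would pass unnoticed. Direction and size are unknown.

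The matter is worth correcting because it governs what the study may claim about its comparator, and because a better analysis is available from information the article says is collected.

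**What to change.** 1. Estimate concordance in operated women who entered on imaging, stating explicitly that women who entered through previous surgical staging are not counted.
2. Report it separately by imaging entry criterion: persistent cyst, and deep disease or other hallmarks such as an obliterated pouch.
3. Standardise it to the conservative group's mix of imaging findings, and of baseline symptoms where recorded.
4. Add a simple sensitivity analysis of the main comparison over a range of predictive values in the conservative group, since standardisation cannot reach unmeasured differences.
5. Replace the closing claim of the sentence quoted from the Exclusion criteria section with a statement that the observed concordance applies to operated women, and that the standardised estimate for the conservative group corrects only for measured features.

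Cost: analysis and wording only. The Interventions section already provides for systematic recording of imaging and prior surgical findings and for collecting operative reports. The price is a reported concordance that is less precise, because it is split by criterion and reweighted, and that may be lower.

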#### Study groups

Participants are allocated to one of two management groups prior to conception: a preconception surgery group (n=350) or a planned non-surgical (conservative) management group (n=350). Within each management group, participants will be subdivided by conception method into a natural conception subgroup (n=200 in each of the surgical and conservative management groups) and an ART (ART/IVF) subgroup (n=150 per preconception management group). Participants may contribute multiple attempted conception cycles, and to both natural and ART cycles.

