Laparoscopic surgery to remove endometriosis exposes women to surgical risks. Surgery could be justified if there is a potential benefit, either in symptom reduction or with improved fertility. Current evidence suggests that patients with deep endometriosis may have improvements in pain symptoms following surgery, particularly after colorectal surgery.^19^ In the group of patients who do not experience significant pain and would be considering surgery to optimise fertility alone, further evidence is needed before the risks of surgery can be justified. Moreover, the issue of future fertility is a vexed question for many women with endometriosis, and the known association with infertility raises questions about whether pre-emptive surgical treatment of endometriosis will provide future benefit with improved pregnancy rates, particularly with regard to risk of adhesions, prevention of disease progression and reductions in ovarian reserve.^20
21^

In recent years, there has also been an increase in research focused on the association between endometriosis and pregnancy outcome.^22–24^ It is possible that the presence of endometriosis, or history of a prior diagnosis of endometriosis, may be associated with poor pregnancy outcomes^25–27^ including placenta praevia, preterm birth, premature prelabour rupture of membranes, obstetric haemorrhage, gestational hypertensive disorders, fetal growth restriction and perinatal death.^28^ It is unknown whether the obstetric outcome risk is ameliorated by prepregnancy surgery for endometriosis or if there is a surgically untreatable factor which underpins the likely increased risk of adverse obstetric outcomes.^9^

Ultimately, our proposed study aims to compare fertility outcomes among four groups of participants with evidence of moderate-severe endometriosis (EMSE):

Those pursuing natural conception without prior surgery.Those pursuing ART without prior surgery.Those undergoing surgery followed by attempts at natural conception.Those undergoing surgery followed by ART.

Cross-comparisons are planned across all four groups.

This study will explore the impact of surgical treatment of moderate to severe endometriosis on pregnancy and live birth rates (LBRs) from both natural conception and in vitro fertilisation (IVF). Obstetric and perinatal outcomes will be assessed as secondary outcomes. In addition, it will seek to clarify whether pre-emptive surgical treatment of endometriosis has an impact on future fertility.

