### Interventions

Participants will complete an initial patient questionnaire focusing on demographic and fertility data. This baseline data are collected and managed using REDCap electronic data capture tools hosted at The University of Melbourne.^29
30^ REDCap is a secure, web-based software platform designed to support data capture for research studies, providing (1) an intuitive interface for validated data capture; (2) audit trails for tracking data manipulation and export procedures; (3) automated export procedures for seamless data downloads to common statistical packages and (4) procedures for data integration and interoperability with external sources. Additional clinical information will be collated by the research assistant team, ensuring systematic documentation of endometriosis imaging and/or prior surgical findings, prior fertility investigations (if relevant) and choice of management pathway.

A mobile phone application (known as an ‘App’) has been developed as a data collection tool specific to this study—the ELFS App. The original App was free for participants to download from the Apple App Store and Google Play (December 2021—November 2024). A newly developed version of the ELFS App is designed as a Progressive Web App which is installed on the participants’ mobile device as an application but is deployed by, and retains the functionality of, a website. Transition to the new App occurred over a fortnight period in November 2024. Participant data and survey responses from the first system were exported, then custom scripts used to transform and validate the information before importing it into the new App platform.

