### Power calculation and planned analysis

The target sample size was determined by a simulation-based power calculation. Data were simulated based on a mixed effects logistic regression model with a single fixed effect for treatment and a single random effect for participant. Different random effect SD of 0.5, 0.7 and 0.9 were considered, based on previous studies reporting random effects with SD around 0.7.^36^ Simulations used 5 cycles per participant for natural conception and 3 cycles per participant for IVF. For each set of simulation parameters, 1000 data sets were generated, mixed effects logistic regression models were fitted, and the power was calculated as the proportion of models where the p value for the main effect was below 0.05. The simulation was done using R V.4.0.2, with the glmmTMB package used to fit the mixed effects logistic regression models.

Natural conception based LBR of 1.4% per cycle has been reported in women with moderate to severe endometriosis and 12 months of unsuccessfully trying.^37^ An increase to at least 4% is needed to be clinically significant.^6^ A sample size of N=400 (200 per arm) would achieve over 90% power under the scenarios considered.

An IVF conception-based LBR of 12% per cycle has been reported in women with moderate to severe endometriosis.^38^ An increase to 20% would be needed to be clinically significant. A target sample size of N=300 (150 per arm) would achieve a power of 82% to 87% under the scenarios considered.

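### The Introduction describes the comparators as women with no prior surgery, but eligibility and group definitions admit previously operated women to either group, and the analysis does not name prior surgery

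*Protocol article*

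**What the plan says.** The Introduction lists four groups. The two comparators are "Those pursuing natural conception without prior surgery" and "Those pursuing ART without prior surgery".

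The Study groups section defines the groups that will be compared as "a preconception surgery group (n=350) or a planned non-surgical (conservative) management group (n=350". This says what is planned from entry and is silent on earlier operations.

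The Inclusion criteria give two routes to the diagnosis. The imaging route asks for disease currently present on ultrasound or MRI. The surgical route is "Presence of untreated moderate or severe endometriosis (rASRM stages 3 or 4) on a previous diagnostic laparoscopy/laparotomy", and only here does the word untreated appear. The text after the exclusions explains why imaging can stand in for surgical confirmation: "a pragmatic decision was made to use expert pelvic ultrasound and/or MRI to identify participants with imaging evidence of moderate–severe disease".

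There are four exclusions. One concerns ability to understand the consent information, and the others read "Do not wish to have future fertility.Findings suspicious of malignancy on expert imaging.Current pregnancy". Previous endometriosis surgery is not among them.

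Under Interventions, the research team collates clinical information, "ensuring systematic documentation of endometriosis imaging and/or prior surgical findings". The analysis section adjusts for duration of infertility, age, obstetric history, male factor and some comorbidities. Prior endometriosis surgery is not named.

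**The concern.** The study asks whether surgery before pregnancy improves fertility. Take a woman who had an endometrioma excised some years ago, now has a recurrence on imaging and plans no further operation. As written she is eligible and belongs to the conservative group, although she has had the kind of surgery under study. If she chooses another operation she joins the surgery group, where first and repeat procedures count as one exposure.

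The contrast actually estimated could then be first or repeat surgery against no further surgery. A null result might be reported as no fertility benefit of surgery when some comparators had already had it. A positive result might be inflated if recurrent disease carries a poorer prognosis. Allocation is not randomised, so nothing in the design balances surgical history between the groups.

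**Working it through.** **Who can enter.**

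| Section | Condition on earlier therapeutic surgery |
|---|---|
| Introduction, list of groups | Comparators have had no prior surgery |
| Inclusion criteria, imaging route | None |
| Inclusion criteria, laparoscopy route | Disease must be untreated |
| Exclusion criteria | None |
| Study groups | None |
| Planned analysis | Not a named confounder |

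The same part of the article says that diagnostic laparoscopy without treatment is uncommon. It is therefore plausible that women with an earlier laparoscopy were treated and now enter by imaging. That gives no share.

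**Direction of bias.** Let p0 and p1 be the per-cycle live birth rates of never-operated women without and with surgery. Let f and g be the shares of previously operated women in the conservative and surgery groups, and r0 and r1 their rates. The observed difference is

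[(1-g)p1 + g r1] - [(1-f)p0 + f r0],

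so the bias relative to p1 - p0 is g(r1 - p1) - f(r0 - p0). The article gives none of f, g, r0 or r1. With g = 0, the bias is negative (dilution) if r0 > p0 and positive (exaggeration) if r0 < p0. With g above 0, the balance between groups matters too.

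**The plan's own power.** Inputs from the power section:
- Natural conception: 200 per arm, 5 cycles, 1.4% against 4%.
- IVF: 150 per arm, 3 cycles, 12% against 20%. The 12% is attributed to the disease stage only: "An IVF conception-based LBR of 12% per cycle has been reported in women with moderate to severe endometriosis".
- Participant random-effect SD 0.5, 0.7 and 0.9; p below 0.05, taken as two-sided.

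This mixed logistic model was simulated with 1000 data sets per scenario, the rates taken at a random effect of zero, and a Wald test. It gave 96.4%, 97.0% and 97.5% for natural conception (stated: over 90%) and 86.8%, 84.9% and 81.3% for IVF (stated: 82% to 87%). The stated figures reproduce.

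**Illustration of dilution.** Assume a share f of the conservative group keeps the whole surgical benefit (r0 = p1) and g = 0. The difference shrinks to (1-f)(p1 - p0). At f = 20%:
- natural: 0.8 × (4 - 1.4) = 2.08 points instead of 2.6;
- IVF: 0.8 × (20 - 12) = 6.4 points instead of 8.0.

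Across the three SDs, power at f = 20% is then 83-85% (natural) and 60-68% (IVF).

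Power at SD 0.7 for f = 10 / 20 / 30%:

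| Handling and assumption | Natural | IVF |
|---|---|---|
| All kept, full carry-over | 92 / 85 / 72% | 77 / 65 / 54% |
| All kept, half carry-over | 97 / 92 / 89% | 81 / 77 / 75% |
| All kept, quarter carry-over | 98 / 96 / 95% | 85 / 83 / 81% |
| Share f removed from both arms, not replaced | 96 / 92 / 90% | 80 / 79 / 72% |

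The first row used 600 data sets per scenario and a Wald test; the others used 500 and a likelihood-ratio test. Monte Carlo error is up to about 2 points (for 80% power and 500 data sets, √(0.8 × 0.2/500) = 1.8 points).

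For IVF, restriction has more power than keeping everyone under full carry-over, about the same under half, and less under a quarter.

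**The case against.** The best defence is that prior in the Introduction means before the conception attempt within the study. The comparators are listed beside women who have surgery and then try to conceive, and Study objectives and Study groups use the same time frame. The Secondary outcomes contrast leaving the qualifying disease in place with excising it. On that reading a woman with an untreated recurrence is a properly classified comparator. The reading is tenable, so this is an ambiguity and not a flat contradiction. It does not settle the matter: the contrast becomes first or repeat surgery against no further surgery, which is not the question in the Abstract and Discussion, and the text still needs to say which is meant.

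It is also fair that the confounder list is introduced as inclusive, that surgical history is collected, and that a fuller plan may use it. The absence of one covariate would not be a finding alone. It matters here because eligibility and group definitions, which the article does set out, leave the gap open. The cohort is deliberately pragmatic, so limiting the primary analysis to never-operated women is a choice and not a necessity.

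A reader might infer that the conservative group does contain operated women, that the surgery effect is therefore diluted, and that IVF loses some 20 points of power. The documents do not support this. They permit such women but give no count. The direction depends on unknown rates, and the Introduction itself raises reduced ovarian reserve. The 20-point loss needs both an assumed 20% share and full carry-over in women who, by eligibility, have moderate or severe disease again.

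**Conclusion.** The point holds as a mismatch between the comparator described and the groups formed. As written, women with earlier therapeutic surgery and recurrent disease can enter either group, and no stated analysis separates them. Neither their number nor the direction of the bias can be read from the article.

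The power figures are conditional illustrations. At an assumed 20% share in the conservative IVF group, power is about 60-70% with full carry-over, 77% with half and 83% with a quarter. Natural conception at the same share is 83-85%, 92% and 96%. All assume no previously operated women in the surgery group. It would also be wrong to infer that excluding these women always gains power; that fails when carry-over is small. The case for separating them is interpretability and control of bias in a non-randomised comparison.

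**What to change.** 1. Reconcile the Introduction with Inclusion criteria and Study groups: state, for each group, whether earlier excisional or ablative endometriosis surgery is allowed, and distinguish it from a purely diagnostic laparoscopy.
2. Include prior therapeutic endometriosis surgery as a stratifier or covariate in both primary live birth comparisons. A covariate alone does not turn the pooled contrast into surgery versus no surgery, so step 3 is also needed.
3. Report the contrast separately for women without prior therapeutic surgery (first surgery versus none) and with it (repeat surgery versus no repeat). Base any conclusion about surgery versus no surgery on the former.
4. State the power achieved in the never-operated stratum.

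The cost is mainly wording, since prior surgical findings are already documented. The one check needed is that the record separates diagnostic from therapeutic procedures for every participant, including those who enter by imaging. The downside is less precision in the never-operated stratum. If 20% of both arms were previously operated, 160 per arm (0.8 × 200) and 120 per arm (0.8 × 150) would remain, with power at SD 0.7 of about 92% (natural) and 79% (IVF).
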